# The efficacy and safety study of dietary supplement PURIAM110 on non-insulin taking Korean adults in the stage of pre-diabetes and diabetes mellitus: protocol for a randomized, double-blind, placebo-controlled, and multicenter trial-pilot study

**DOI:** 10.1186/1745-6215-12-38

**Published:** 2011-02-11

## Abstract

**Background:**

Diabetes has already become a threat to the nation and the individual due to its high prevalence rates and high medical expenses. Therefore, preventing diabetes at an earlier stage is very important. Despite advances in antidiabetic agents, we have not yet achieved any satisfying results in treating diabetes. Among various treatments, medicinal herbs and supplements for diabetes are reported to show generally good efficacy and safety data. In particular, PURIAM110, a compound from orange fruits and mulberry leaves, is supposed to prevent the progress of type II diabetes mellitus and improve diabetic symptoms. This is the first reported pilot study about the protective effect of the orange fruits and mulberry leaves mixture against pre-diabetes on Korean adults. Based on these positive results of herb-derived components, extended studies of dietary supplements have to be done to suggest confirmative evidences.

**Methods/Design:**

The efficacy and safety study of PURIAM110 is a double-blinded, placebo-controlled, randomized, and multi-center clinical trial. A total of 45 subjects will participate in this study for 6 weeks.

**Discussion:**

The present protocol will confirm the efficacy and safety of PURIAM110 for pre-diabetes, suggesting more basic knowledge to conduct further randomized controlled trials (RCT). In addition, PURIAM110 can be an alternative dietary supplemental remedy for diabetes patients.

**Trial Registration:**

ISRCTN: ISRCTN44779824

## Background

Pre-diabetes is a condition of potential diabetes mellitus with an increased risk of developing type 2 diabetes [1,2]. In other words, it is a state of either impaired fasting glucose (IFG) or impaired glucose tolerance (IGT). Pre-diabetes is asymptomatic in many occasions, but once it develops into type 2 diabetes, it makes patients suffer from polydipsia, polyuria, polyphasia, unusual weight loss, and extreme fatigue [3]. Unmanaged chronic diabetes mellitus affects quality of life and induces life-threatening diabetes-associated complications [4,5]. Its mortality rate cannot be ignored in Korea, becoming the fourth leading cause of death by 2030 [6]. According to the Korean National Health and Nutrition Survey (KNHNS) 2001, prevalence rates of diabetes were 1.4 million (8.1%) in Korean men and 1.3 million (7.5%) in Korean women. Nowadays, it is reported that about 308 million people worldwide are having impaired glucose tolerance (IGT) and among them 25% to 75% will develop diabetes [7,8]. Since the exact figures of Korean pre-diabetes patients and diabetes progressing rates were not reported [4], we can deduce from the above numerical statement that a considerable population *must be *at the status of potential diabetes. Socioeconomic expenditures are also high, at 193 million won per year for medication [4,9]. Therefore, preventing and treating efforts for the non-insulin taking patients in the stage of pre-diabetes and diabetes are urgently needed to lift the burden from both the nation and patients [10]. Even though novel remedies have been produced unceasingly, most of them seem to be often ineffective for this disease [11,12]. Meanwhile, dietary supplements are known to be relatively effective in treating diabetes, with few adverse effects [13-15]. Among 400 reported herbal medicines for diabetes [16], recent studies suggests that bitter oranges and mulberry leaves have antidiabetic effects. PURIAM110, a compound made from orange fruits and mulberry leaves (patent application no. 10-2006-0020040), is expected to prevent the progress to the early stage of diabetes mellitus, safely [17,18]. Bitter orange is a dried, immature fruit of *Citrus aurantium L*., used from ancient times to remove the stagnation and distension in hypochondriac regions [19,20]. Like other herbal components, its mechanism of action seems to be complex though, the fruit has been identified to produce antihyperglycemic activity. Mulberry leaf is a dried leaf of *Morus indica L*., which also shows hypoglycemic properties [21,22]. It has been prescribed widely to dispel wind-heat and heat in the lung [23,24]. Relying on pathophysiologic mechanisms from traditional Korean medicine, diabetes can be caused when there is heat in the lung or a deficiency of energy (Yang qi) and body fluid. Therefore, bitter orange's qi driving activity and mulberry leaf's heat dispelling function in the lung can be applied to play an antidiabetic role.

Despite the advantages of herb-derived supplements, few RCTs have been conducted [8,25], and the bitter oranges and mulberry leaves compound is not an exception. Further trials of dietary supplements have to be done to suggest confirmative evidence.

The aim of this study is to evaluate the efficacy and safety of the PURIAM110, a dietary supplement for the treatment of patients with pre-diabetes and diabetes mellitus non-insulin dependent stage [26]. This paper is the first pilot study with orange fruits and mulberry leaves on Korean adults who are at the status of pre-diabetes and diabetes mellitus not in the insulin requiring stage. The results of this study will give us the clinical of biochemical parameters, such HbA1c, fructosamine, fasting glucose and 2-h OGTT glucose between the placebo and PURIAM110 groups. On the basis of the results, we can suggest the optimal design, precise sample size, and primary outcome for a further large scale RCT.

## Methods/design

### Objectives & Hypothesis

#### Objectives

The primary objective of this pilot study is to assess the efficacy and safety of PURIAM110 on non-insulin taking Korean adults in the stage of pre-diabetes and diabetes mellitus.

The secondary objective is to estimate the precise sample size and primary endpoint required for the large scale RCT.

#### Hypothesis

We hypothesize that glucose concentration of pre-diabetes and diabetes mellitus who are treated with PURIAM110 will be lower than that of the control group. Also, we expect that other diabetes related parameters (total cholesterol, triglyceride, and LDL cholesterol) to be improved and the symptoms to be normalized in the treatment group.

### Study design

This is a 6-week, double-blinded, placebo-controlled, randomized, and multi-center clinical trial assessing the efficacy and safety of PURIAM110.

The study has been conducted in two Oriental Medical Hospitals in Korea from December 2006.

Figure 1 provides an overview of the study.

**Figure 1 F1:**
[figure not shown]
**Study flowchart**. Summary of the study flow.

### Population

The Korea Food & Drug Administration (KFDA)'s rule recommends including not only healthy group but also a sub-health condition population when conducting dietary supplement trials. Therefore, we included pre-diabetes status, and diabetes mellitus non-insulin dependent stage Korean adults, aged 18 to 65. The detail inclusion and exclusion criteria are described in Table 1 and Table 2.

**Table 1 T1:** Inclusion criteria. Inclusion criteria of the PURIAM110 trial

Inclusion criteria	
1.	Both gender between the ages of 18-69 years, eligible for study through screening test prior to the enrolment.
2.	Able and willing to perform the study protocol and participate throughout the entire trial period(Screening, baseline, 3, 6 weeks, follow up(if needed)).
3.	Participants who understood the risks and benefits of the study and signed a written informed consent.
4.	Among individuals not under diabetes mellitus treatment, whose random glucose concentration is 110~250 mg/dL measured with Accu-Chek^®^(Roche, Germany) glucometer within 3 weeks prior to participation.
4.1.	fasting plasma glucose concentration is 100-190 mg/dL or
4.2.	2- hour plasma glucose concentration* is 130-250 mg/dL( * venous plasma glucose 2-hour after ingestion of 75 g oral glucose load; DIASOL-S LIQ. [Glucose] Taejoon Pharm.)

**Table 2 T2:** Exclusion criteria. Exclusion criteria of the PURIAM110 trial

Exclusion criteria	
1.	Presently using other blood glucose level controlling agents.
2.	History of allergy to the herbal products (bitter oranges and Mulberry leaves) or allergic diseases such as asthma.
3.	Medication (within the last 1 month or during the study) which would affect the study results.
4.	Daily intake of alcoholic beverages.
5.	Smokers consuming more than 1 pack/day.
6.	Presently having acute diseases or other untreated illness requiring treatment.
7.	Impaired hepatic or renal functions.
8.	Pregnant, breast feeding status or female of reproductive age, not using proper contraception.
9.	Participant in other clinical trials or a blood donor, within the past 1 month.
10.	History of severe disease or any condition, in the investigator's opinion, that would endanger the individual's safety or affect the study result.
11.	Patients diagnosed as type I and type II diabetes mellitus(insulin requiring stage).

### Inclusion and exclusion criteria

#### Inclusion criteria

Inclusion criteria are as follows (Table 1).

#### Exclusion criteria

Exclusion criteria of PURIAM110 trial are summarized in Table 2.

#### Suspension criteria

• Administration of forbidden medicine.

• Subject's demand to discontinue the study.

• Serious adverse events (AE) or unusual changes in clinical test results.

• Principal investigator's decision to terminate the study (low rates of compliance, complications, or unable to sustain the study for various reasons).

### Sample size

We had difficulties in determining adequate sample size, as preliminary studies were insufficient. So we adopted a pilot study design.

Two points had to be considered in deciding the sample size. One was the special condition of herb-derived dietary supplements regulatory law in Korea, and another was limited research fund. Since herbs have historical efficacy and safety profile in Korea, KFDA regulates dietary supplements under a different rule, compared to conventional drugs. In other words, as the efficacy and safety of herbal products have been clinically validated for a long time, the regulatory authorities have lightened restrictions, such as minimizing sample size. We have planned the dietary supplement study according to this KFDA rule. The KFDA rule prescribes that when designing a dietary supplements trial, the sample size has to be a minimum 30 per group. Therefore we first fixed the number of the subjects in the treatment group as 30.

As the research funding was restricted, we plan to allocate 15 individuals for the placebo group. When sample size is inevitably restricted, it is considered to be more ethical by the KFDA to set more subjects in the test group than in the control group. In conclusion, a total of 45 subjects will be recruited in this pilot study.

### Randomization

The study subjects will be randomly assigned to either PURIAM110 or placebo group at a ratio of 2:1, according to the 'random number table' generated by SAS software package (SAS institute, Inc, Carey, NC, USA, version 8.2).

### Blinding

The study drugs are double blinded to both investigator and subject. The contract research organization (CRO; Kyung Hee University, Center for Clinical Research and Genomics) of the sponsor, labels the investigational drugs by the randomization code number. The labeled experimental products will be provided to the trial sites by the CRO.

### Interventions

#### Treatment drug

PURIAM110 is a 460 mg hard gelatin capsule, containing dried powder of bitter oranges and mulberry leaves (Table 3). The dried powder is made of hot water extraction of bitter oranges and mulberry leaves 1:1 mixture followed by spray drying. The raw material extract is provided by SunTen pharmaceutical company (SUN TEN PHARMACEUTICAL Co., LTD.) in Taiwan.

**Table 3 T3:** Constituents of PURIAM110. Constituents of the PURIAM110

PURIAM110 (460 mg/1 hard gelatin capsule)
bitter oranges (zhi shi, *Fructus Aurantii*; the unriped fruits of *Citrus aurantium L*.)
mulberry leaves (sang ye, the dried leaf of *Folium Mori*)
Sodium Silica Aluminate (lubricants)

#### Constituents of PURIAM110

The constituents of PURIAM110 are in Table 3.

#### Placebo

The placebo will contain the lactose. And the placebo will be manufactured to have a similar appearance, shape, weight (460 ± 10 mg/1 capsule), taste, and color with PURIAM110 [27].

#### Directions

The subjects will be prescribed for total 6 weeks, 2 times per day (3 capsules before breakfast and 3 capsules before dinner). Participants will take total 6 capsules daily, with a dose of 2,760 mg (460 ± 10 mg/1 capsule × 6 capsules).

### Study groups

1. Treatment group: PURIAM110.

2. Control group: placebo.

### Study period

The study period will be of 42 days (total 6 weeks). The visits and the evaluations will be done at the screening (visit1), 0th day (visit2; baseline), 21th day (visit3; 3rd week), and 42nd day (visit4; 6th week). 56th day is a follow up (if needed).

### Outcomes

#### Efficacy assessment index

##### Primary outcome index

1. Biochemical parameters:

1.1. HbA1c

1.2. Fructosamine

1.3. Fasting glucose

1.4. 2-h OGTT glucose

1.5. Fasting insulin

1.6. Total cholesterol

1.7. Triglyceride

1.8. Low density lipoprotein (LDL) cholesterol

##### Secondary outcome index

1. Diabetes symptoms*

1.1. polydipsia

1.2. polyuria(frequent urination)

1.3. polyphasia

1.4. fatigue

2. Other clinically significant parameters**

3. Anthropometric parameters:

3.1. body weight(kg)***

3.2. waist circumference(WC, cm)

3.3. hip circumference(HC, cm)

The primary and secondary outcomes will be measured at the 0th day (visit2; baseline), the 21th day (visit3; 3rd week), and the 42nd day (visit4; 6th week) during the treating period. And, when necessary, the outcomes will be assessed at the 56th day (follow-up). The changes between the 0th day (visit2; baseline) and the 42nd day (visit4; 6th week) measurements will be analyzed for the primary outcome indexes. For the secondary outcomes, a visual analogue scale (VAS) will be used to detect the improvement of diabetic symptoms (*). When the scale has improved more than two grades or a patient has recovered completely from these symptoms, it will be evaluated as 'effective'. For other categories (**), we will assess whether these parameters have normalized or not. Measured weight minus 0.5 kg (participant's garment weight) will be recorded as the subject's true weight (***).

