### Measurement tools

#### Visual analogue scale (VAS)

A 10 cm VAS (ranging from 0 cm as no symptom to 10 cm as the maximum symptom) will be used to assess diabetic symptoms (polydipsia, polyuria, polyphasia, and fatigue) improvement during treatment term.

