### Statistical analyses

#### Efficacy analysis

All analyses in this study will be based on both intention-to-treat (ITT) and per protocol (PP) method. The ITT method will include all randomized subjects who made at least one next visit. The participants who have completed the 6-week treatment without major protocol violations and kept compliance rate over 80% will be analyzed by the pp (per protocol) method. The continuous variables will be summarized as mean±SD (standard deviation) and the categorical variables will be described in frequency and percent. For the primary and secondary outcome variables, the mean differences between before (visit 2; baseline) and after the treatment (visit 4) values will be compared using the paired t-test or Wilcoxon test, in each group. The baseline characteristics will be compared by either the Student t-test for the continuous variables or χ^2^-test for the categorical data (alternatively, Fisher's exact test will be used if the expected value is less than 5 or McNemar's test for non-normal distribution data). The efficacy of PURIAM110 will be assessed by using the independent t-test (when normality assumption is satisfied, alternatively Mann-Whitney test will be used). All analyses will be based on a two-sided test at a 5% significance level. With values of p < 0.05 will be considered statistically significant. SPSS for windows version 12.0 (SPSS Inc., Chicago, Illinois) will be used for analyses. For missing values, 'Last Observation Carried Forward (LOCF)' method will be applied.

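### Symptom response is defined in undefined 'grades' on a continuous 10 cm VAS, counts any fall to zero as a response, and is not ranked against the mean VAS change

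*Protocol article*

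**What the plan says.** The Secondary outcome index lists four symptoms (polydipsia, polyuria, polyphasia, fatigue) and gives a responder rule for them: "When the scale has improved more than two grades or a patient has recovered completely from these symptoms, it will be evaluated as 'effective". Under Measurement tools the instrument is described thus: "A 10 cm VAS (ranging from 0 cm as no symptom to 10 cm as the maximum symptom) will be used to assess diabetic symptoms". Table 4 schedules the VAS at screening, baseline, visit 3 and visit 4.

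The Efficacy analysis section treats all outcomes as before-and-after values. Within each group, "the mean differences between before (visit 2; baseline) and after the treatment (visit 4) values will be compared using the paired t-test or Wilcoxon test", and this covers secondary as well as primary outcomes. Between groups, "The efficacy of PURIAM110 will be assessed by using the independent t-test (when normality assumption is satisfied, alternatively Mann-Whitney test will be used". The chi-square and Fisher tests appear only in the sentence that begins "The baseline characteristics will be compared by either the Student t-test for the continuous variables".

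Table 1 sets no symptom requirement for entry, and the Background states: "Pre-diabetes is asymptomatic in many occasions".

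**The concern.** Three features of the symptom outcome do not fit together.

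- **Unit.** The rule counts grades and the instrument has none. Whoever analyses the data must choose what a grade is, and that choice fixes the response rate.
- **Recovery route.** Reaching zero counts whatever the starting value, so a trivial fall is a response. A subject who starts at zero has nothing to improve or recover from. Entry does not require symptoms, so such subjects can be enrolled.
- **Which outcome.** The Outcomes section gives a yes/no result for symptoms, while the Efficacy analysis section gives a mean change. Neither is ranked first. It is also unclear whether the rule applies to each symptom separately or to all four together.

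At stake is a symptom response rate that can move with a decision taken after the data are seen and that can count negligible changes as benefit.

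**Working it through.** **Plan's own figure.** The only sample-size figure is 30 + 15 = 45, with 30/15 = 2:1, and it reproduces. No power, response rate, VAS mean or VAS SD is given, so the calculations below rest on labelled assumptions.

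**Step 1: units side by side.** The rule asks for more than two grades. The scale is "A 10 cm VAS (ranging from 0 cm as no symptom to 10 cm as the maximum symptom". No section divides the line into grades.

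**Step 2: how much the undefined cut-off matters.** Let D be the improvement in cm from visit 2 to visit 4, assumed normal with mean 0.5 and SD 2 (illustrative only; a real VAS is bounded). If one grade is g cm, the grade route needs D > 2g, so

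P(response) = 1 − Φ((2g − 0.5)/2).

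| g (cm) | cut-off 2g (cm) | (2g − 0.5)/2 | P(response) | expected among 45 |
|---|---|---|---|---|
| 0.1 | 0.2 | −0.15 | 56% | 25.2 |
| 1 | 2 | 0.75 | 22.7% | 10.2 |
| 2 | 4 | 1.75 | 4.0% | 1.8 |
| 2.5 | 5 | 2.25 | 1.2% | 0.5 |

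The same data give a response rate anywhere from about 1% to 56%.

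**Step 3: the recovery route.** Write the rule as (V2 − V4 > c) or (V2 > 0 and V4 = 0), where V2 and V4 are the VAS at visits 2 and 4. Take c = 2 cm, that is, a grade of 1 cm (assumed).

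- 0.3 to 0 is a fall of 0.3 cm: a response, by recovery.
- 9 to 7 is a fall of 2 cm: not a response, because 2 is not more than 2.
- Starting at 0, neither condition can be met.

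The second case alone is only the boundary that any cut-off has. The defect lies in the contrast with the first case. If the rule is limited to subjects with V2 > c, a fall to 0 always exceeds c and the two routes no longer conflict.

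**Step 4: which outcome.** The Outcomes section ties the day 0 to day 42 change to the primary indexes and gives symptoms the responder rule. The Efficacy analysis section opens its comparison with "For the primary and secondary outcome variables, the mean differences between before". Both symptom results are therefore in the plan, without precedence.

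**Step 5: are the named between-group tests usable on a yes/no result?** All 31 × 16 outcomes for 30 versus 15 subjects were enumerated, and the binomial probabilities of those with p < 0.05 were summed.

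| common response rate | t-test or Mann-Whitney | Fisher |
|---|---|---|
| 5% | 0.039 | 0.010 |
| 10% | 0.036 | 0.021 |
| 20% | 0.045 | 0.030 |
| 30% | 0.050 | 0.033 |
| 40% | 0.048 | 0.031 |
| 50% | 0.046 | 0.029 |
| 60% | 0.048 | 0.031 |

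No type I error exceeds 5%. Power at 60% versus 20% (assumed rates) is 0.74 for the t-test or Mann-Whitney and 0.67 for Fisher.

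**The case against.** The best defence is that the Efficacy analysis section already analyses the VAS as a continuous change between visits 2 and 4 and names a between-group test that is not limited to primary outcomes. Much of this stands, and it rules out several stronger readings that a reader might infer.

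- **No valid between-group test exists.** This is not supported. The independent t-test or Mann-Whitney test suits the VAS change, and Step 5 shows that it holds its error rate even on a 0/1 result. What remains is that no categorical test is tied to the responder result. On its own, that detail could sit in an analysis plan that is not shown.
- **Dichotomising reduces 45 subjects to about 29.** That figure (2/π × 45 = 28.7) applies to a normal outcome split at its median with the continuous data discarded. The plan does not discard them.
- **Symptom-free subjects dilute the response difference to 70–40% of its value.** This assumes that 30–60% have no symptom at baseline, and the article gives no such figure. Subjects at zero would dilute the mean change as well, so the responder rule is not the cause. The same Background sentence goes on to say that symptoms appear once type 2 diabetes develops, and the trial also enrols subjects with diabetes.
- **The four symptom outcomes become uninterpretable.** Only the responder result is affected.

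It is also fair to say that a journal article condenses, and the full protocol may define a grade. But here the article states the rule in one unit and the instrument in another. That is a conflict in the stated text, beyond mere omission.

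**Conclusion.** The point holds in limited form. The responder rule cannot be applied as written, because its unit does not exist on the stated scale. Its recovery route counts trivial falls, and the text does not say which symptom result leads. The first two follow directly from the wording. The size of the first, about 1% to 56% response, depends on the assumed mean of 0.5 cm and SD of 2 cm and on the range of grade widths tried. How many subjects the recovery route affects is unknown, since no baseline symptom data are given. That response would reflect baseline severity more than treatment is plausible but not shown.

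The importance is minor to moderate. These are secondary outcomes in a pilot, and the Discussion says that the later trial's primary outcome will be chosen from the glucose and lipid parameters, so symptom response is not a candidate.

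**What to change.** 1. For each of the four symptoms, name the change in VAS (cm) from visit 2 to visit 4, compared between groups with adjustment for baseline VAS, as the symptom outcome.
2. Keep 'effective' as a supportive result only. State its cut-off in cm, fixed before unblinding, and apply it to each symptom separately, in subjects whose baseline for that symptom exceeds the cut-off.
3. Compare the responder proportions by a named categorical test such as Fisher's exact test. If unblinding has already taken place, report any cut-off in cm as chosen post hoc.

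The cost is mainly wording, since the VAS is already recorded in cm at the visits needed. The supportive analysis will use fewer subjects. If 30–60% had no symptom at baseline (assumed), at most 15 × 0.7 = 10.5 down to 15 × 0.4 = 6 placebo subjects would remain. Fisher's test is also conservative at this size: with all 45 subjects, 80% power needs about 66% versus 20% response, and fewer subjects would need a larger difference. A mean change is a less simple headline than a response rate.
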